### 5.1. Outcome Measures

Dichotomous Outcomes: The frequency of outcomes will be determined, and we will utilize time-to-event analyses. The hazard ratios (HRs) along with their 95% confidence intervals (CIs) will be determined using a stratified Cox proportional hazards model.Continuous Outcomes: The differences between the intervention and control groups, along with their 95% CIs and corresponding *p*-values, will be documented.

Both patient-level and cluster-level data will be analyzed. We will address any imbalances in individual data by adjusting statistically using a mixed-effects Cox regression model performed by a statistician blinded to the group allocation. 

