## 10. Limitations 

The blinding of participants is not feasible for this trial due to the nature of the intervention. While the non-blinded design may introduce bias in outcome assessment [41], care has been taken to mitigate bias through cluster randomization and ensuring that outcome assessors are assigned to only one study group over the intervention period. 

The 90-day intervention period may not capture long-term effects on wound healing, potentially missing essential insights into the sustainability and long-term impact of the intervention. Hence, outcome measurements at 6 months and 1 year and an economic evaluation alongside the cluster RCT have been planned to determine if this intervention period is adequate.

The focus on community settings in Singapore may also affect the generalizability of the results to other healthcare systems. However, as pressure injury management requires an extended period of care and is generally not managed within a fixed healthcare setting and environment, the findings will contribute to evidence-based management, improving patient outcomes and healthcare cost-effectiveness. The study’s potential impact on policy and practice, considering the unique healthcare financing and reimbursement landscape in Singapore for nutritional intervention [14], adds to its relevance and importance.

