## Figures and Tables

**Table 1 nutrients-16-00299-t001:** Exclusion criteria for the INCA Trial.

	Exclusion Criteria
1.	Septicaemia.
2.	Poorly controlled diabetes (*glycated hemoglobin level > 8.5%)* [20,26].
3.	Consumption of supplements will lead to fluid intake in excess of fluid restriction for the following conditions: Advanced renal disease not on dialysis (KDIGO [21,22] Stage G4 with an eGFR of 15–29 mL/min/1.73 m^2^ and Stage G5 with an eGFR of less than 15 mL/min/1.73 m^2^); Heart failure with reduced ejection fraction [27]; Advanced decompensated alcoholic and non-alcoholic liver cirrhosis [28,29].
4.	Current neoplastic disease or last chemotherapy or radiotherapy less than one year ago.
5.	Currently on immunosuppressive therapy.
6.	Palliative with *a lifespan of ≤ 3 months.*
7.	Known allergy reaction to L-arginine or phenylketonuria.
8.	Presence of an infected wound *(if it is the only pressure injury present on the participant).*
9.	Untreated diagnosed osteomyelitis [18,19,30,31,32].
10.	Pregnant women and children (there is limited evidence on the use of arginine in these groups).

**Table 2 nutrients-16-00299-t002:** Outcomes and the methods of measurement to be used in the cluster RCT.

Type	Outcome	Outcome Description	Measurement Method	Data Collection Time Point (t) and Time Frame	Performed by
Primary	Wound	Change in the area of pressure injury (cm^2^) from the baseline	Assessed by the change in wound area ^#^ from the baseline to the follow-up time points and measured with a 3D wound imaging device at the time of follow-up.	t_0_ baseline, t_1_ 30 days, t_1_ 60 days, t_3_ 90 days, t_4_ 6 months, and t_x_ 1 year Time frame: 1 year	Nurse
		The proportion of participants with ≥40% area reduction	Assessed by the number of participants with wound area ^#^ reduction ≥ 40% at the time of follow-up versus the baseline.	t_1_ 30 days, t_1_ 60 days, t_3_ 90 days, t_4_ 6 months, and t_x_ 1 year Time frame: 1 year	Nurse, CRC
Secondary	Wound	The proportion of participants with complete wound healing of the main wound	Assessed by the number of participants with complete healing of a wound ^#^, determined by clinical assessment and pressure injury staging.	t_1_ 30 days, t_1_ 60 days, t_3_ 90, t_4_ 6 months days, and t_x_ 1 year Time frame: 1 year	Nurse, CRC

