	Clinical	Mortality	Assessed by the occurrence and time-to-event of all-cause mortality during the study period.	t_1_ 30 days, t_1_ 60 days, t_3_ 90 days, and t_x_ 1 year Time frame: 1 year	Nurse, CRC
		Unplanned hospital admissions	Assessed by the occurrence and time-to-event of one or more unplanned hospital admissions during the study period.	t_1_ 30 days, t_1_ 60 days, t_3_ 90 days, and t_x_ 1 year Time frame: 1 year	Nurse, CRC
Others	Pre-specified Outcome	Adherence to nutrition Supplementation intake	Assessed by the number of participants with >75% consumption of oral nutritional supplements and Arginaid, where the servings of products consumed are counted with confirmation of intake during follow-up.	t_1_ 30 days, t_1_ 60 days, and t_3_ 90 days Time frame: 1 year	Dietitian, Nurse, CRC
		Wound depth	Measured (millimeters) using sterile forceps and rulers at follow-up.	t_0_ baseline, t_1_ 30 days, t_1_ 60 days, 90 t_3_ days, and t_x_ 1 year Time frame: 1 year	Nurse
		Hospital length of stay	Assessed by the number of days for each unplanned hospital admission.	If available: t_x_ 1 year Time frame: 1 year	Nurse, CRC
		Wound duration and time-to-heal	Measured by days to complete healing for participants with complete wound healing. Additional interaction of time with intervention and other covariates will be included and tested	t_x_ 1 year Time frame: 1 year	Investigators
		Frequency of unplanned hospital admissions	Assessed by the frequency of occurrence per participant and the sum of unplanned hospital admissions of all participants.	t_x_ 1 year	Investigators

^#^ The data from the measurement of the pressure injury with the highest severity will be used in the analysis for the primary endpoint. If the wound of the highest severity is deemed unmeasurable (e.g., too small of a surface area), we will select the wound with the next highest severity. CRC: clinical research coordinator; HRQOL: health-related quality of life; PI: pressure injury.

**Table 3 nutrients-16-00299-t003:** Study schedule of enrolment, interventions, and assessments.

	STUDY PERIOD							
	Enrollment	Allocation	Post-Allocation					Close-Out
TIMEPOINT	*−7 to −1d* −*t_0_*	Baseline *t_0_*	*30d t_1_*	*60d t_2_*	*90d t_3_*	*6m t_4_*		*1y* *t_x_*

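### Cox regression on visit dates attenuates a real effect on the wound outcomes, more so after day 90 when the visit gaps widen; a grouped-time or interval-censored model avoids this at little cost

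*Protocol article*

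**What the plan says.** **Model.** Section 5.1 sends dichotomous outcomes to time-to-event analysis: "The frequency of outcomes will be determined, and we will utilize time-to-event analyses". Hazard ratios "will be determined using a stratified Cox proportional hazards model", and a mixed-effects Cox model is planned for adjustment.

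**Ascertainment.** Table 2 defines the ≥40% response by status at a visit: "Assessed by the number of participants with wound area ^#^ reduction ≥ 40% at the time of follow-up versus the baseline". The listed times are "t_1_ 30 days, t_1_ 60 days, t_3_ 90 days, t_4_ 6 months, and t_x_ 1 year Time frame: 1 year". Complete healing has the same schedule ("t_1_ 30 days, t_1_ 60 days, t_3_ 90, t_4_ 6 months days, and t_x_ 1 year"), as does increased severity. Table 3 places wound imaging and staging at these visits only. Section 3.2 allows ±14 days around each visit. Section 8.1 lists baseline, 30, 60 and 90 days and 12 months for wound data, without 6 months.

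**Use of the late visits.** The intervention lasts 90 days (section 2.1). In the Table 2 row on wound duration and time-to-heal, under Others, the plan says: "Additional interaction of time with intervention and other covariates will be included and tested". Section 10 says that the 6-month and 1-year measurements, together with the economic evaluation, "have been planned to determine if this intervention period is adequate".

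**The concern.** An outcome judged at visits is known only to have occurred between two visits. A Cox model treats the recorded visit date as the event date. In a long gap, participants who responded early stay in the risk set until the next visit, and many events in both arms are recorded close together. The estimated hazard ratio then moves from the true value towards the ratio of the proportions with an event in that interval, which lies closer to 1.

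The gaps widen exactly when the intervention stops, so a constant effect can look weaker after day 90. True waning is also plausible at that point, and a Cox fit to visit dates cannot cleanly separate the two. This touches the time-by-intervention test for time-to-heal, and any reading of late hazard ratios as evidence on whether 90 days is enough.

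**Working it through.** **Inputs from the protocol.** Visits at 30, 60, 90, about 182 and 365 days give gaps of 30, 30, 30, about 92 and about 183 days. The visit window is ±14 days. The planning odds ratio is 2.0, and enrolment is 190 per arm (section 2.4). The plan gives no figure on this point to reproduce, and section 2.4 states no control rate.

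**Assumptions.** Control response by day 90 is 40%. This is one value at which an odds ratio of 2.0 gives the stated 144 per arm (with continuity correction, at about 40 to 42%). The true hazard ratio is constant over the year.

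**Step 1: true hazard ratio.** Control odds are 0.40/0.60 = 0.667. Doubled, they are 1.333, so the intervention proportion is 1.333/2.333 = 0.571. Under proportional hazards, HR = ln(1 − 0.571)/ln(1 − 0.40) = 0.847/0.511 = 1.66. The control hazard is 0.511/90 = 0.00568 per day.

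**Step 2: mechanism, one gap at a time.** Suppose every event in a gap carries the same date. With Breslow ties, the Cox estimate for that gap is exactly p1/p0, the ratio of interval proportions among those still at risk. Here p0 = 1 − exp(−0.00568 × gap) and p1 = 1 − exp(−0.00568 × 1.66 × gap).

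| Gap (days) | p0 | p1 | p1/p0 | ln(1−p1)/ln(1−p0) |
|---|---|---|---|---|
| 30 | 0.157 | 0.246 | 1.57 | 1.66 |
| 92 | 0.407 | 0.579 | 1.42 | 1.66 |
| 183 | 0.646 | 0.821 | 1.27 | 1.66 |

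The last column is what a complementary log-log model estimates. It does not depend on the length of the gap.

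**Step 3: with ±14-day scatter.** Simulation with Efron ties, with the hazard after day 90 at 100%, 50% or 25% of its earlier value, gave Cox hazard ratios of about 1.65 to 1.67 up to day 90 and 1.49 to 1.59 after it. The complementary log-log model gave about 1.66 to 1.69 in both periods. With nominal dates, Breslow ties and an unchanged hazard, Cox gave 1.58 early, 1.38 late and 1.48 overall.

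**Step 4: sensitivity to event rate and tie method.** True hazard ratio 2.0, constant hazard, estimates up to v after day 90. The first two columns are large-sample values; the last is from simulated trials of 190 per arm.

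| Control rate by day 90 | Breslow, nominal dates | Efron, nominal dates | Efron, ±14 days |
|---|---|---|---|
| 15% | 1.95 v 1.77 | 2.00 v 1.98 | 2.02 v 1.88 |
| 30% | 1.89 v 1.59 | 2.00 v 1.92 | 2.00 v 1.72 |

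Efron ties help on nominal dates but not once dates scatter. Few events then share a date, yet responders awaiting their next visit are still counted as at risk. Two checks identify the cause. With 30-day gaps kept after day 90, Breslow gives 1.89 v 1.89 in the 30% case, and exact event dates give 2.01 v 2.03.

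**Step 5: false waning at the planned size.** In trials of 190 per arm with 30% dropout and true hazard ratios of 1.5 or 2.0, a z-test of early against late hazard ratios falsely showed significant waning in 1.5 to 9% of trials, against a nominal 2.5%. With a hazard ratio of 1.66 and ±14-day scatter it was 6.8%, 5.0% and 3.3% at later hazards of 100%, 50% and 25%.

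**Step 6: if section 8.1 governs.** Without the 6-month visit, the time after day 90 is one gap of 365 − 90 = 275 days. In the 30% case with a true hazard ratio of 2.0, the late estimate on nominal dates falls to 1.34 (Breslow) or 1.75 (Efron).

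**The case against.** - **The passages are not joined in the plan.** The time-by-intervention text stands in one row, for time-to-heal, and names neither a model nor a split at day 90. It is not attached to the ≥40% response. This stands: for that primary outcome, the consequence is an attenuated overall hazard ratio.
- **Section 10 can be answered in other ways.** Proportions at each visit and changes in area are not distorted by the spacing, and the plan reports frequencies too. This stands. The concern reaches section 10 only where hazard ratios are used to answer it.
- **The bias is small beside sampling error.** At a true hazard ratio of 1.66 the overall Cox estimate was 1.56 to 1.64, with a log hazard ratio standard error of 0.12 to 0.13. Since ln(1.66/1.56) = 0.06 and ln(1.66/1.64) = 0.01, the bias is about 0.1 to 0.5 standard errors. This stands.
- **Healing dates may be finer.** Assessments take place at home nursing visits (section 3.1) and time-to-heal is counted in days, so dates between study visits might exist. This is unresolved. Tables 2 and 3 schedule none, and the ≥40% response needs the scheduled imaging.
- **It is detail for the analysis plan.** Tie handling would be. The Cox model, however, is a choice stated in section 5.1, so it can be reviewed here.

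**Conclusion.** The concern holds as a modest bias in a stated model. Cox on visit dates attenuates a non-null hazard ratio, and the widening gaps make this stronger after day 90. Under the 40% control rate and a true hazard ratio of 1.66, the late estimate is about 1.49 to 1.59 and the overall estimate about 1 to 7% low. The effect is small at event rates of about 10 to 20%, which matters if complete healing is uncommon, and larger with Breslow ties on nominal dates. The event rates, the hazard shapes and the constant true effect are assumptions, because the protocol gives none of them.

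A reader might infer that apparent waning is built into the design and will be reported. The documents do not support that. The distortion needs a real effect and depends on the event rate and tie handling, and in these scenarios fewer than one trial in ten showed false significant waning. A reader might also infer that the primary comparison is invalid. It is not: with no effect there is no distortion, so this mechanism does not inflate its type I error.

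This is a cheap improvement, not the correction of a serious error.

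**What to change.** 1. In section 5.1, for wound outcomes ascertained at visits (≥40% reduction, complete healing, increased severity), replace Cox with a grouped-time complementary log-log model. Use one baseline term per visit interval and keep the planned cluster random effect. An interval-censored proportional hazards model is an equivalent choice. Both still report a hazard ratio.
2. In Table 2, test time by intervention for time-to-heal within that model.
3. Keep Cox for death and unplanned admission, where exact dates are recorded.
4. Reconcile section 8.1, which omits the 6-month wound assessment, with Tables 2 and 3, which include it.

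The cost is a change of wording and a different standard model, with no extra data or participants. The downside is slightly wider intervals for the late-period effect.

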### 3.1. Primary Outcome Measurements 

Change in Pressure Injury Area from the Baseline: Measurement of the alteration in the surface area of the identified pressure injury (PI) at identified time points;Proportion of Participants with 40% or Greater Area Reduction: Calculation of the percentage of participants who exhibit a reduction in the PI area by at least 40% at the same time points.

For participants with multiple PIs, the most severe or largest same-stage PI will be selected for primary analyses. Data from additional PIs will contribute to secondary analyses. Assessments and treatment documentation will be conducted during scheduled home nursing visits. Both objective and patient-reported outcome measures are used for the secondary outcome measurements to ensure that crucial additional information is collected from the participant’s perspective. 

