### 3.2. Secondary Outcome Measurements

Proportion with Increased Severity in Pressure Injury Stages: The percentage of participants whose pressure injury progresses in severity (PI stage and area of wound);Proportion with Complete Pressure Injury Healing: The percentage of participants whose PIs fully heal;Proportion with Improvement in Health-Related Quality of Life (HRQOL): The percentage of participants showing enhancements in HRQOL, as measured by the standardized instrument EQ-5D-5L;Proportion with Nutritional Status Improvement: The percentage of participants with measured nutritional advancements;Change in HRQOL (EQ-5D-5L Utility Values and VAS): The measured alteration in HRQOL utilizing EQ-5D-5L utility values and Visual Analog Scale (VAS);Incidence of New PIs: The number of new PIs during the study period;Incidence of PI Wound Infections: The number of new infections in PI wounds during the study period;Mortality Rate: The death rate among participants during the study time frame;Unplanned Hospital Admissions and Length of Stay (LOS): The frequency and duration of unexpected hospital admissions within the participant group.

All the study data and outcome measurements listed in Table 2 will be recorded using the Research Electronic Data Capture (REDCap) system [34]. Sociodemographic data will be collected based on recommendations by a local systematic review of healthcare utilization in urban Singapore [35]. 

A window period of ±14 days will be implemented for all assessments and outcome measurements. If an outcome measurement is interrupted (e.g., malfunction of wound imaging equipment, secure cloud server downtime, or assessors unable to visit on the day of assessment due to participant’s request for postponement), the assessor will re-attempt the measurement within the window period. Any outcomes measured outside of this window period will be considered a protocol deviation. 

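### The only between-group comparison named for the ≥40% area-reduction primary is a Cox hazard ratio, which does not match the by-visit proportion that defines the outcome or the odds ratio that sizes the trial, and does not measure whether a response lasts.

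*Protocol article*

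**What the plan says.** **Definition.** Section 3.1 of the protocol article gives the binary primary outcome as: "Calculation of the percentage of participants who exhibit a reduction in the PI area by at least 40% at the same time points". Table 2 words it as a "reduction ≥ 40% at the time of follow-up versus the baseline" and lists 30, 60 and 90 days, 6 months and 1 year. The co-primary is continuous: "Measurement of the alteration in the surface area of the identified pressure injury (PI) at identified time points".

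**Sample size.** Section 2.4 uses an odds ratio of 2.0 for ≥40% improvement in area, with 80% power and two-sided 5% error, and arrives at 144 per arm.

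**Analysis.** For dichotomous outcomes Section 5.1 says: "The frequency of outcomes will be determined, and we will utilize time-to-event analyses". Hazard ratios with 95% confidence intervals "will be determined using a stratified Cox proportional hazards model", and imbalances are handled by a mixed-effects Cox model. No exception is made for the ≥40% outcome. For continuous outcomes the same section promises group differences with confidence intervals and p-values.

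**Purpose of the late visits.** Section 2.1 sets 90 days of intervention and one year of outcome collection. Section 10 concedes that 90 days may be too short, "potentially missing essential insights into the sustainability and long-term impact of the intervention", and gives this as the reason for measuring at 6 months and 1 year.

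**Other reversible outcomes.** Section 3.2 also lists complete healing, nutritional improvement and, for quality of life, "The percentage of participants showing enhancements in HRQOL, as measured by the standardized instrument EQ-5D-5L".

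**The concern.** A ≥40% reduction is a state, not a terminal event. A wound can meet the threshold at day 30 and fail it at 6 months. Under the definition in Section 3.1 that participant is a responder at the first visit and a non-responder at the second. Under an ordinary Cox analysis the participant has the event at day 30 and contributes nothing afterwards.

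The definition, the sample size and the model for one primary outcome therefore describe different quantities: a proportion at a visit, an odds ratio for that proportion, and a rate of first crossing. The difference matters here because the intervention stops at day 90. Whether its effect lasts is a question the plan itself raises, and the headline binary comparison would not answer it.

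**Working it through.** **1. The plan's own figure.** Section 2.4 gives no control response rate, so 144 cannot be confirmed from the stated inputs alone. It can be reached for a comparison of two proportions. With OR 2.0 and an assumed control rate of 0.40:

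- Intervention rate = 2 × 0.40 / (0.60 + 2 × 0.40) = 0.571.
- Pooled two-proportion formula: 133 per arm. With continuity correction: 144 per arm.
- Other control rates with continuity correction: 35% gives 147, 45% gives 145, 50% gives 148.

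The stated figure is thus consistent with a test of two proportions at one time, which is the quantity in Section 3.1 and not the one in Section 5.1.

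**2. The scales are not interchangeable.** If 40% v 57.1% were cumulative response under proportional hazards with complete follow-up, the hazard ratio would be ln(1 − 0.571) / ln(1 − 0.40) = (−0.847) / (−0.511) = 1.66, not 2.0.

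**3. What each measure does with relapse.**

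| Participant | By-visit status (Section 3.1, Table 2) | Ordinary Cox (Section 5.1) |
|---|---|---|
| Meets 40% at day 30, holds to 1 year | Responder at every visit | Event at day 30 |
| Meets 40% at day 30, lost by 6 months | Responder early, non-responder at 6 months and 1 year | Event at day 30 |

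The hazard ratio treats the two participants identically.

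**4. Illustration.** The control rate and relapse rates are assumptions; the documents give neither. Let p be the proportion who ever respond and r the share of them who have relapsed by 1 year. Status at 1 year is p(1 − r). With 40% v 57.1% ever responding (OR 2.0):

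| Relapse, control v intervention | Status at 1 year | OR at 1 year | OR, ever responded |
|---|---|---|---|
| 10% v 10% | 36.0% v 51.4% | 1.88 | 2.0 |
| 10% v 25% | 36.0% v 42.9% | 1.33 | 2.0 |
| 10% v 40% | 36.0% v 34.3% | 0.93 | 2.0 |

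For the second row: 0.40 × 0.90 = 0.360; 0.571 × 0.75 = 0.429; OR = (0.429/0.571) / (0.360/0.640) = 0.750/0.5625 = 1.33.

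The arms are equal at 1 year when 0.571 × (1 − r) = 0.36, that is r = 37% in the intervention arm.

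The result varies only moderately with the control rate. With the same 10% v 25% relapse:

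- 30% v 46.2% ever responding gives 27.0% v 34.6% (OR 1.43).
- 50% v 66.7% ever responding gives 45.0% v 50.0% (OR 1.22).

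**The case against.** **First-event coding is inferred.** Section 5.1 does not mention a first event, does not say that a responder leaves the risk set, and gives no rule on relapse. The analysis plan, which is not shown, may define the event. This stands in part: event definitions are commonly left to that document. But first-event coding is the ordinary reading of a Cox model, and the article names no recurrent-event or multistate alternative. The conflict between a by-visit proportion and a hazard ratio is in the article's own text, and an analysis plan that followed Section 5.1 would inherit it.

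**A reader might infer that sustainability cannot be judged at all.** The documents do not support that. Outcome frequencies are to be determined, the ≥40% proportion is tabulated at 6 months and 1 year, and change in area is a primary outcome at those visits, compared between groups with confidence intervals and p-values. Regrowth would be visible there. Likewise, quality of life is also analysed as change in EQ-5D-5L scores up to 1 year. What is missing is a between-group comparison of the binary primary that registers relapse: the frequencies carry no contrast, interval or test.

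**A reader might also infer that repeated visits create false responders through measurement error and so cost power.** The documents give no variability for the 3D imaging device, so no size can be put on this. Under assumed log-scale SDs of 0.10, 0.15, 0.20 and 0.30, an unchanged wound crosses the threshold at least once in five visits in 0.07%, 3.3%, 12.4% and 32.3% of cases. Single-visit status shares part of the same error (3.6% to 11.4% at SDs of 0.20 to 0.30). No power loss is claimed.

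**Nor is it necessary to require that every response be confirmed at the next visit.** A day-90 response would then have to persist to 6 months, in a trial that assumes 20% mortality and 10% withdrawal, and the event would be conditioned on later survival.

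**Conclusion.** The point holds as a mismatch. The only comparative measure stated for the ≥40% primary is a hazard ratio, while the outcome is defined as a status at each visit and powered as an odds ratio for a proportion. Read in the ordinary way, the hazard ratio says how soon the threshold is first met and nothing about whether the response lasts beyond the 90-day intervention.

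The size depends on relapse rates that the documents do not give. In the illustration, the odds ratio at 1 year falls from 2.0 to 1.33 with 10% v 25% relapse, and to 0.93 with 10% v 40%, while the ever-responded contrast does not move. If relapse is rare or similar in the arms, the practical difference is small (OR 1.88 at 10% in both). The mismatch with the definition and the sample size remains whatever the relapse rate.

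**What to change.** Reconcile Sections 2.4, 3.1 and 5.1 and Table 2:

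- Make the between-group comparison of ≥40% status at named visits the analysis of the binary primary. Name one visit as primary (for example day 90, when the intervention ends) and report 6 months and 1 year alongside it.
- Express it as an odds ratio or risk difference from a model that allows for clustering by postal code. Count a participant who has relapsed as a non-responder at that visit.
- Treat complete healing, improved quality of life and improved nutritional status the same way, at the visits at which each is scheduled.
- Keep Cox regression for events such as death and first unplanned admission, and at most as a supportive time-to-first-response analysis of the ≥40% outcome.

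**Cost.** This needs wording and programming. Tables 2 and 3 already schedule the wound visits, but the list in Section 8.1 omits 6 months and should be aligned. The main binary comparison gives up information on how early a response occurs. Participants without a measurement at the named visit, including those who die before it, need a stated rule; Section 2.4 assumes 20% mortality and 10% withdrawal, so that rule will matter.
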